## Abstract

**Background:**

Malnutrition is a huge problem in Burundi. In order to improve the provision of services at hospital, health centre and community levels, the Ministry of Health is piloting the introduction of malnutrition prevention and care indicators within its performance based financing (PBF) scheme. Paying for units of services and for qualitative indicators is expected to enhance provision and quality of these nutrition services, as PBF has done, in Burundi and elsewhere, for several other services.

**Methods:**

This paper presents the protocol for the impact evaluation of the PBF scheme applied to malnutrition. The research design consists in a mixed methods model adopting a sequential explanatory design. The quantitative component is a cluster-randomized controlled evaluation design: among the 90 health centres selected for the study, half receive payment related to their results in malnutrition activities, while the other half get a budget allocation. Qualitative research will be carried out both during the intervention period and at the end of the quantitative evaluation. Data are collected from 1) baseline and follow-up surveys of 90 health centres and 6,480 households with children aged 6 to 23 months, 2) logbooks filled in weekly in health centres, and 3) in-depth interviews and focus group discussions. The evaluation aims to provide the best estimate of the impact of the project on malnutrition outcomes in the community as well as outputs at the health centre level (malnutrition care outputs) and to describe quantitatively and qualitatively the changes that took place (or did not take place) within health centres as a result of the program.

**Discussion:**

Although PBF schemes are blooming in low in-come countries, there is still a need for evidence, especially on the impact of revising the list of remunerated indicators. It is expected that this impact evaluation will be helpful for the national policy dialogue in Burundi, but it will also provide key evidence for countries with an existing PBF scheme and confronted with malnutrition problems on the appropriateness to extend the strategy to nutrition services.

**Trial registration:**

ClinicalTrials.gov PRS Identifier: NCT02721160; registered March 2016

## Background

### Malnutrition

Malnutrition is a huge problem worldwide. In 2010 about 115 million children worldwide were underweight, 55 million had low-weights-for-height and 171 million under the age of five years had stunted growth. Over the last decades, progress has been achieved. The proportion of children under the age of five years in developing countries who were underweight is estimated to have declined from 29 % to 18 % between 1990 and 2010. Yet, this rate was inadequate to meet the Millennium Development Goal 1, Target 1.C of halving levels of underweight between 1990 and 2015 [1].

Many of the challenges the global community faces in its fight against malnutrition are present in Burundi, one of the poorest countries in the World (with a GDP estimated at PPP $ 770 in 2014 [2]): 58 % of children under five years old suffer from chronic malnutrition and 6 % from acute malnutrition. Young children are particularly vulnerable: 10 to 11 % of the children aged 6–18 months were found to be acutely malnourished in 2010 [3].

These poor figures result from many factors. Food security is a major problem in the country. The majority of the population lives in rural areas. The high population density and overall poverty put pressure on land use, constrain investment and affect agricultural productivity. The landlocked nature of Burundi and its very weak economy also limit financial and geographic access to food markets. This results each year in food deficits: in 2009, the daily average food ratio was 1600 kcal per inhabitant (while FAO and WHO recommendations are between 2000 and 2600 kcal, depending on age and gender). Children from the poorest households stand greater risk to be undernourished, than their counterparts in the most privileged households.

Another constraint is the low performance of the health system in addressing malnutrition, both on prevention and care aspects. With its partners, the Ministry of Health (MoH) implemented in 2010 a national protocol [4] with a new care approach of acute malnutrition that proposes a plan of treatment and follow-up of malnourished children to be integrated within the formal health system (i.e. health centres (HC) and hospitals). However, to date, only one third of HCs and half of hospitals provide malnutrition care services. Another problem is the dependency on technical and financial partners, mainly UNICEF and the World Food Program (WFP) who provide nutritional inputs on an unstable basis^1^. There are also constraints at facility level, such as weak stock management capacities.

Before developing this research protocol, we conducted a rapid assessment of the services at the HC level. We observed an overall neglect of nutrition services at all levels and noticed a lack of knowledge among health workers (HW) involved in nutrition activities, limited motivation among them and among community health workers (CHW), as well as weak supervision ([name] and [name], unpublished observations).

### Health care financing in Burundi: the key role of PBF

Malnutrition is of course only one of the many health challenges faced by the population of Burundi. Constraints are tight, as the government has very limited resources. Still, the government of Burundi made major efforts over the last years to raise the health of the poor and most vulnerable groups.

A key milestone was the removal of user fees for children under five and deliveries implemented in May 2006. In 2006, Burundi also piloted Performance-Based Financing (PBF) in three provinces. The strategy rapidly gained popularity and in April 2010, PBF was scaled up to the whole country. By doing so, Burundi became the second country in Africa to implement PBF in the health sector nationwide (after Rwanda) and the first to use the PBF system to correct the malfunctions related to the implementation of the national free health care policy [5].

Today, all public and most private non-profit health facilities in the country—HCs and hospitals—are covered by the national PBF scheme. The program is governed by the ‘*Cellule Technique FBP*’, a technical group of the MoH. The Burundian PBF system reflects the main health priorities of the country and rests on contractual arrangements involving different parties: every month health facilities report their activities related to the incentivised indicators; these reports are reviewed and validated at the province level and then sent to the *Cellule Technique FBP* which approves transfers of subsidies to the health facilities. The completion of this process takes between two and three months [6]. In addition, these activities are semi-annually randomly checked by community based organizations contracted to verify (via community surveys) the truthfulness of activities reported by HC [7]. Besides, qualitative indicators are used quarterly to assess the quality of the working environment and taken into account as bonuses or penalties for the amount of PBF subsidies transferred to each facility. The national PBF program is financed from several sources, with the Government and the World Bank (WB) being the largest and second largest sources of funding respectively.

There is a strong conviction in Burundi that the national PBF scale-up improved national health care financing, in terms of coherence, governance and vision [5]. Over the years, evidence has accumulated to support the policy [8–10], even if many questions remain. PBF has been put forward as a possible strategy to improve coverage rates of high impact interventions, quality of care, efficiency and overall performance of the health system [11–14]. PBF is a very recent policy innovation; the evidence base is growing, but is still very limited [15, 16]. A Cochrane review has concluded that the available evidence was too limited to ascertain the effectiveness of PBF in LMICs [17].

### PBF extended to nutrition indicators

#### Design and roll-out of the PBF nutrition intervention

To tackle the challenge of malnutrition and provide malnourished children with the most appropriate care, the MoH decided in 2013 to add nutrition indicators to the existing PBF scheme. A systemic strategy being needed, it was decided to incentivise three levels of services: the district hospitals, the HCs and the CHWs, on both prevention and care aspects, with a focus on children below five years old.

The PBF indicators related to nutrition follow the standard model in Burundi, and come as a combination of quantitative indicators to encourage an increase in service delivery and coverage rates (see Table 1) and qualitative indicators to stress the importance of improving the quality of services to ensure a positive outcome for the user [18]. Quality of nutrition activities is assessed quarterly, and a bonus or penalty is applied to subsidies received by the facilities according to their quality score: a facility with a score above 80 % will receive a bonus equivalent to the score multiplied by 25 % of the nutrition PBF subsidies; while a facility with a score below 60 % will be subject to a penalty of 10 to 25 % of the nutrition PBF subsidies. The verification of activities related to nutrition PBF indicators is also included in the usual verification system (see above).

**Table 1 Tab1:** Quantitative indicators

Community level	(1) screening and referring of acute malnutrition cases to HCs, (2) organizing classes promoting good food and nutrition behaviours, and (3) organizing cooking practice classes.
Health centre level	(1) screening and caring severe and moderate acute malnutrition cases of children below five years old, or screening and referring acute malnutrition cases of children below five years old (depending on the type of HC^a^), and (2) growth follow-up and promotion for children below two years old.
Hospital level	(1) the number of treated severe acute malnutrition cases with medical complications of children below five years old and (2) the length of the stay at the hospital.

Note: ^a^Most of HCs do not provide care services for acute malnutrition cases and do have to refer cases to HCs that provide this type of care

Regarding the indicators at the community level, pre-verification of quantitative nutritional services provided is done by the HCs who supervise the CHWs, on the basis of registers and reports provided by them. The process of verification and validation is completed at the provincial level.

#### Implementation

It was jointly decided by the MoH and the WB that this addition of nutrition indicators to the existing PBF system deserved to be rigorously evaluated. The research design incorporates a randomized control component as far as HCs are concerned (see below for more details). It was decided that HCs in the control group would receive financial compensations equivalent to the PBF subsidies received in the intervention group (weighted average, considering volume of activities, staff).

As shown in the Fig. 1, all hospitals with nutrition services fall under the Nutrition PBF program. Regarding HCs, we distinguish two types: nutritional HCs, i.e. HCs delivering the full package of nutrition services, and HCs that do not provide these services but instead refer acute malnutrition cases to the former. In the intervention group, both types of HCs are subject to the new nutrition indicators applied to PBF; while in the control group, both of them receive an input-based financing compensation. At the community level, the CHW groups that refer to the nutritional HCs are subject to the nutrition PBF in the intervention group while those in the control group will not receive any compensation due to budget constraints [18].

**Fig. 1 Fig1:**
[figure not shown]
The PBF Nutrition Scheme. ‘PBF Nut’ means ‘Under PBF Nutrition programme besides the existing PBF scheme’ while ‘Comp Nut’ means input based financing compensation besides the existing PBF scheme

The intervention at nutritional HC and hospital levels started in January 2015, involving 45 nutritional HCs and 29 district hospitals with the extended PBF scheme, as well as 45 nutritional HCs with the compensation scheme (control group). The interventions in the other type of HCs as well as at the CHW level were expected to start in summer 2015, but due to major political instability since April 2015, they have started respectively only in January 2016 and in October 2015.

#### Theory of change

The introduction of nutrition activities into the PBF program translates policy makers’ belief that PBF can trigger some positive changes in the performance of the health personnel, facilities or system which will eventually impact on households and children. We have identified seven tracks for transmission of effects for the health facility performance:**The income track**: the injection of extra financial resources might have a positive effect on nutrition services, as it allows the health facility manager to recruit more staff, to better equip his facility, etc.**The cash track**: the fact that the financial resources are transferred directly to the health facility’s bank account allows the latter to rapidly and autonomously spend.**The incentive track**: the extra resources are conditioned upon higher performance in nutrition activities; this should motivate community actors and staff to improve their performance in order to boost the health facility’s income and theirs (if bonuses are distributed among HWs). At facility level, the effect on other services is unclear: it can be negative for some (e.g. if the staff in charge of nutrition used to be responsible for other services which are now overlooked, as they are relatively less financially rewarding) and positive for others (if there are economies of scope—i.e. dedicating efforts to nutrition activities, reduce efforts required for other activities, thanks to synergies).**The information track**: through the contract, the fee system and the related information sessions, staff have a clearer view on what performance should be, as far as nutrition services are concerned. Feedback from the program may also guide their decisions to improve. We hypothesize a positive effect on nutrition services. However, as for the incentive track, a negative effect could be that activities which are not remunerated may be perceived as non-important.**Supervision & enforcement track**: under the new scheme, verification is extended to nutrition activities; this means that there will be more interaction between supervisors and the personnel in charge of nutrition. On top of the possible subsequent transfer of information (e.g. advice on good practices), the supervision may activate interpersonal motivators.**Culture at provider level track**: a PBF scheme invites health facility managers to develop a work culture more favourable to innovation, flexibility, responsibility and entrepreneurship. As PBF has been a national policy for five years, one can assume that this is already the case in Burundi. However, one cannot exclude that it could positively influence the nutrition department more.**Health system track**: it has been argued that PBF can trigger several system effects [16]. Here, part of these effects might come from the supervisors of the impact evaluation (e.g. the MoH requesting UNICEF and the WFP to better supply nutrition inputs; the WB solving some problems which may affect the study). Another part might come from the health facilities themselves (e.g. pressure upon the Department for Nutrition within the MoH to be a more reliable and responsive supplier). We expect that CHWs will refer more malnourished children to HCs and HCs will refer more SAM children to referral hospitals. This may trigger some unexpected feedback loops.

For an overview of the expected results chain of the introduction of nutrition criteria in the PBF grid, see the Fig. 2.

**Fig. 2 Fig2:**
[figure not shown]
Results chain of the introduction of nutrition criteria in the PBF grid

There is also a specific theory of change for the control HCs. The main design difference between the intervention and control groups is the formula to obtain the extra funding: each HC of the intervention group has to improve its own performance to increase its revenue; control HCs do not have any effort to do: they just have to hope that the intervention group, as a whole, will be performing. This choice for the definition of the two groups to compare indicates that the main causal path under investigation is the incentive one. Other tracks are not denied (see the qualitative part of the research) but are considered as secondary Table 2.

**Table 2 Tab2:** Routes applying in the Intervention and Control groups at the facility level

	Intervention group	Control group
(1) Income	++	++ ^a^
(2) Cash	++	++ ^a^
(3) Incentive	++ on nutrition services ? on other services	~
(4) Information	++	+ ^b^
(5) Supervision & enforcement	++	? ^c^
(6) Culture at provider level	~ or +	~ or + ^d^
(7) Health system	++	? ^e^

Notes: Symbols + and ++ mean that routes apply moderately to strongly; ? means unclear, ~ means neutral ^a^The control HCs will get additional financial resources which will correspond to a weighted average of the nutrition subsidies received in the intervention group. ^b^Before the start of the intervention, all 90 HCs were provided with some information on the nutrition indicators and on their performance in nutrition services. ^c^In a district where there are control and intervention HCs, the district team supervisors may transfer good practices to both intervention and control HCs. ^d^Control HCs know that there will probably be a scale up of the nutrition indicators to all HCs after the pilot; some managers may anticipate this by already reorganizing their nutrition services. ^e^Some health system effects might affect control HCs (e.g. if there is a problem of availability of nutritional inputs at national level, because of the pressure by intervention HCs, the supply to control HCs may be reduced)

## General objectives and research questions

The overarching objective of our research is to assess the effects of the introduction of criteria focusing on malnutrition prevention and care activities in the existing PBF system. Main research questions at 1) population and 2) HC levels are:Does the introduction of criteria focusing on malnutrition prevention and care activities in the existing PBF system result in a reduction in acute and chronic malnutrition rates in the community?Does the introduction of criteria focusing on malnutrition prevention and care activities in the existing PBF program result in better outcomes at the facility level, i.e. in better management of malnutrition cases (better recovery rates, shorter periods of treatment, etc.)?

In addition, the research incorporates two sub-questions which will allow identifying the possible causes of the success or any disappointing outcome, including unintended side-effects: Table 33)What are the transmission mechanisms induced by the introduction of criteria focusing on malnutrition prevention and care activities in the existing PBF program?4)What are the reasons for the success or failure of PBF on nutrition activities?

**Table 3 Tab3:** Main outcomes for the impact evaluation

Level	Outcomes
Population	- Prevalence of acute malnutrition (defined as WHZ < -2 or MUAC < 125 mm) and of stunting (defined as HAZ < -2) among children aged 6-23 months - WHZ, HAZ and MUAC among children aged 6-23 months
Health Centre	- Recovery rates from MAM and SAM cases of children below five years old - Duration of treatment of MAM and SAM cases of children below five years old

Notes: HAZ stands for Height-for-Age Z-score; MAM for Moderate Acute Malnutrition; MUAC for Mid-Upper Arm Circumference; SAM for Severe Acute Malnutrition; and WHZ for Weight-for-Height Z-score

In addition to these questions, the data collection has been designed in such a way to allow assessment of equity and efficiency of the intervention, potential externalities on other outcomes, and systemic spill-over effects, including possible demand for professional training by the health facilities. These aspects are not covered in this protocol paper.

## Method

This evaluative research adopts a mixed methods design which is increasingly seen as essential in health systems research as it allows researchers to view problems from multiple perspectives, contextualize information, and develop a more complete understanding of a problem [19]. It is also especially important in low- and middle-income country settings, where an in-depth understanding of social, economic and cultural contexts is essential to assess health systems’ performance [20]. With the increasing number of LMICs introducing PBF strategies, other researchers have used mixed methods to assess their impact [21–24].

### The quantitative component

Our main questions (1) and (2) require quantified measures and the possibility to attribute variations in the outcome measures to the intervention. We have opted for a *cluster-randomized controlled evaluation design*, with health centres^2^ as the primary unit of sampling and *sous-collines*^3^ (sub-hills) as the secondary unit of sampling. The 90 selected nutrition HCs were allocated to either a control group (45) or a treatment group (45). For each household survey and around each selected HC, six *sous-collines* are randomly selected; and in each *sous-colline*, 12 households with at least one child aged 6–23 months are surveyed.

#### Sample size and randomization

The sample size of the household surveys is computed on the smallest difference in the main outcome that can be considered of public health significance, i.e. a reduction of about 25 % in acute malnutrition prevalence in intervention centres as compared to control centres. Assuming that the intervention will result in decreasing the prevalence of MAM in children aged 6–23 months from 10 % to 7.5 % [3], and assuming that 65 children aged 6–23 months are to be surveyed in the catchment area of each HC, 90 HCs were needed to be randomized to either the intervention or control group, for an α-error of 5 % and a β-error of 20 %. The number of children per HC was increased to 72 to allow for missing or incomplete data, amounting to a total of 6,480 children aged 6–23 months over the 90 selected HCs. In total, a sample of 6,480 children were surveyed for the baseline, and, two years after the start of the program, another sample of 6,480 children aged 6–23 months will be surveyed.

Selection of HCs invited to participate in the study was done by simple randomization (computer-based random selection) among the 193 eligible HCs, i.e. HCs providing nutrition services (treatment of SAM and MAM). The 90 selected HCs have been paired on essential parameters of organization and functioning in relation to the outcomes (MAM rehabilitation activity, volume of activity, population in the catchment area, and percentage of recovery among malnourished children) as measured during the baseline survey. This will then be used to control for the potential confounding effect of these parameters. Within each of the 45 pairs, allocation to the intervention was done randomly through a lottery system organized by the MoH during a workshop in December 2014.

Simple randomization should be applied to select the households to be surveyed in the catchment area of the 90 HCs. However, such an approach was difficult logistically and could have turned out to be extremely resource-consuming. The chosen alternative option was to sample clusters of households, i.e. households living close to each other. Six clusters of 12 eligible households were selected at random from the whole catchment area of a given HC. This could be done without expanding the overall sample size given the quite high intra-class correlation considered for the sample computation.

The sample size of clinical files within the HC survey was computed on the smallest difference in the main outcome that could be considered of public health significance in intervention centres. Assuming that the intervention will result in increasing the recovery rate of acute malnutrition in children under five years from 80 % to 90 %, for an α-error of 5 %, a power of 80 % and an inter-cluster correlation (ICC) of 0.15 [25], a minimum of 12 clinical files per HC and per nutrition service (MAM and SAM rehabilitation services) were needed, among all children having been registered in the six previous months [26].

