#### Analysis strategy plan

First, some descriptive analysis are carried out in order to understand the main features of malnutrition management and of health services in general in Burundi at the HC level. Validation of the design was performed with the baseline survey data by comparing the treatment group with the control group.

Second, with both survey rounds’ data, the impact of the intervention will be assessed with multilevel statistical models with random effects at the HC level. Continuous dependent variables will be analysed in mixed-effect regression models, whereas categorical ones (e.g. recovery yes/no) will be analysed in logistic regression or Poisson regression models. At the population level, other factors of child malnutrition, such as household food security, socio-economic status, etc., will be controlled for. Interactions with season, child age and sex, stunting, and socio-economic parameters will be analysed. An equity analysis will also be performed in order to understand whether the intervention benefits more the poorer or richer households. At the HC level, other factors of child malnutrition recovery, such as for instance HC staff and CHWs knowledge and know-how, will be controlled for. Interactions with child age and sex, stunting and MUAC will be analysed.

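### Health centres were randomised within 45 matched pairs, but the stated impact model does not carry the pairing through: it names only a health-centre random effect

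*Protocol article*

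**What the plan says.** In the protocol article, the section on sample size and randomization says that the 90 health centres (HCs) were paired on four characteristics from the baseline survey: "MAM rehabilitation activity, volume of activity, population in the catchment area, and percentage of recovery among malnourished children". It then says: "Within each of the 45 pairs, allocation to the intervention was done randomly through a lottery system organized by the MoH". The same section gives the matching a role in the analysis: "This will then be used to control for the potential confounding effect of these parameters". It does not say how.

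The analysis strategy plan of the quantitative component says that "the impact of the intervention will be assessed with multilevel statistical models with random effects at the HC level". At population level it adds that "other factors of child malnutrition, such as household food security, socio-economic status, etc., will be controlled for". At HC level it adds factors of recovery, "such as for instance HC staff and CHWs knowledge and know-how, will be controlled for". The pair is not mentioned there, and neither are the four matching parameters.

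**The concern.** The pair is the unit within which the lottery was held, so it belongs to the structure of the design. A model whose only grouping term is the HC treats the 90 HCs as exchangeable. Variation between pairs, which the allocation balanced across the arms, then stays in the error term.

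If pair members have similar outcomes, the estimated standard error of the treatment effect is too large. The test then rejects less often than its nominal level and some power is given up. The effect should be larger for recovery than for community prevalence. Baseline recovery is itself a matching variable, and at an ICC of 0.15 most of the variance of an HC mean lies between HCs.

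**Working it through.** **Inputs from the protocol article.** Clinical files: recovery 80% vs 90%, α 5%, power 80%, ICC 0.15, 12 files per HC and service. Household survey: prevalence 10% vs 7.5%, α 5%, power 80%, 65 analysable children per HC, no ICC value. Both: 45 HCs per arm.

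**Assumptions.** Two-sided tests. A within-pair correlation r, acting on the between-HC variance, of 0 to 0.5; the article gives none.

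**Step 1: the plan's own sample sizes.**
- Files: an unmatched comparison of 80% with 90% needs 199 per arm. The design effect is 1 + 11 × 0.15 = 2.65. 199 × 2.65 = 527.4, and 527.4 / 12 = 43.9 HCs per arm. With 45 HCs the minimum is 11.2 files, hence 12. The stated figure is reproduced with no allowance for matching.
- Households: an unmatched comparison of 10% with 7.5% needs 2,005 per arm. 45 × 65 = 2,925, a design effect of 2,925 / 2,005 = 1.459. The implied ICC is 0.459 / 64 ≈ 0.007 (about 0.013 if the test were one-sided). This is back-solved, so it cannot confirm the stated size.

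**Step 2: how much pairing can act on.** Between-HC share of the variance of an HC mean:
- Files: 0.15 / (0.15 + 0.85/12) = 0.68.
- Households: 0.0072 / (0.0072 + 0.9928/65) = 0.32.

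**Step 3: the same r under both analyses.** With v = p(1−p), c = 45 and m children or files per HC:
- Variance assumed when pairs are ignored: V = (v₀ + v₁)(ICC + (1−ICC)/m)/c.
- True variance: V − C, where C = 2r·ICC·√(v₀v₁)/c.
- Pairs ignored: critical value t with 88 df (1.99) times √V, while the estimate has standard deviation √(V − C).
- Pairs used: paired t with 44 df (2.02) and standard error √(V − C).

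For files at r = 0.5: V = 0.25 × 0.2208/45 = 0.001227, C = 0.000400, V − C = 0.000827, so √V = 0.0350 and √(V − C) = 0.0288. Pairs ignored: real size 2[1 − Φ(1.987 × 0.0350/0.0288)] ≈ 1.6%, power 85.5%. Pairs used: power 92.5%.

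| Outcome | r | Real size, pairs ignored | Power, pairs ignored | Power, pairs used |
|---|---|---|---|---|
| Files | 0 | about 5% | 80.7% | 79.7% |
| Files | 0.2 | 3.3% | 82.4% | 84.9% |
| Files | 0.3 | 2.7% | 83.3% | 87.6% |
| Files | 0.5 | 1.6% | 85.5% | 92.5% |
| Households | 0 | about 5% | 79.1% | 78.1% |
| Households | 0.2 | 4.0% | 79.8% | 80.7% |
| Households | 0.5 | 3.0% | 81.1% | 84.7% |

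The household rows use an ICC of 0.0073. They start at 79.1% because of that rounding and the t critical value, not because pairs are ignored. The size formula sets a t critical value against a normal tail and gives 4.7% at r = 0, so the sizes shown are slightly low.

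**Step 4: sensitivity to the household ICC.** At 0.02, power is 60.7% (ignored) vs 64.4% (used) at r = 0.2, and 61.9% vs 73.6% at r = 0.5. The starting point is then 60.1% at r = 0, which does not fit the planned 80%.

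**The case against.** The strongest reply is that the pairing has not been forgotten. The sample size section announces that it will be used for control, and an HC random effect is compatible with adding a pair term. The covariate lists are open-ended, the article is a condensed account that also leaves the sous-colline level out of the model, and a separate analysis plan may give the coding. This stands as far as intention goes. A reader might infer that the authors decided to discard the matching, or that the two sections contradict each other; the text supports neither. What remains is narrower. The article does state the model's type, its random-effect level and examples of its covariates. The open lists concern factors of malnutrition and of recovery, and a randomisation stratum is not clearly among them.

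A reader might also infer an underpowered or invalid analysis. That does not follow. The file sample size is reproduced without any gain from matching, the household size is consistent with the same approach, and the error is in the conservative direction.

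It is also tempting to set power with pairs used against the planned 80%. That overstates the gain, because effective pairing reduces the variance of the estimate even when the analysis ignores the pairs. The fair comparison holds r the same in both analyses.

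Two further points stand. The matching variables mostly describe facility activity, so nothing shows that they predict community prevalence well. And both survey rounds are to be used: if the effect is estimated as a change between rounds (an assumption), persistent HC differences are already partly removed and pairing adds less than shown.

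**Conclusion.** The point holds as a gap between two sections: allocation was within pairs, control for the matching parameters is promised, and the stated impact model does not deliver it.

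For r between 0.2 and 0.5, the model as stated forgoes about 2.5 to 7 power points for recovery and about 1 to 4 for household prevalence. For recovery, the test's real size falls to between about 3.3% and 1.6%. If the matching is ineffective (r = 0), using the pairs costs about 1 point. The 80% power and 5% error targets are kept.

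These sizes rest on the assumed r, two-sided testing, the back-solved household ICC, and a comparison of HC means that takes no credit for baseline data. The conservative direction when r is positive is firm; the amount is not. This is a worthwhile, low-cost correction, not a threat to validity.

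**What to change.** In the quantitative analysis strategy plan, state how the pairing enters the impact models at both levels. Either add a pair effect, random or fixed, with HC nested within pair and about 44 degrees of freedom for treatment, or use a within-pair permutation test. Adjusting for the four matching parameters is an acceptable alternative and also meets the promise in the sample size section.

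The cost is one model term and a drop from 88 to 44 degrees of freedom (critical t 2.02 instead of 1.99). A random pair effect has the practical advantage that, if one HC of a pair is lost, the other stays in the analysis. Settling this before the follow-up data are analysed avoids a later choice between paired and unpaired results.
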